### Sample size

We planned to recruit a total of 102 HSAs. Our sample size estimation is based on change in proportions of the primary outcomes expected pre and post intervention. Assuming an alpha of 0.05, 97 HSAs would provide 80% power for a minimum detectable rate of change between 6 and 7% in referral, re-consultation and hospitalizations (one-sided test). We assumed a 1% urgent referral rate, based on the proportion of children identified as needing to be urgently referred at clinics in a previous study conducted in Malawi [11]. As an urgent referral rate of 8% has been estimated as a reasonable consensus referral rate at clinics in sub-Saharan Africa [43, 44] that are correctly adhering to IMCI, we assumed the addition of the SL eCCM App could improve urgent referral rates close to this estimate; a 6–7% change between the control and intervention was, therefore, a conservative estimate of this assumption. Given the short trial duration and potential of perceived elevated status through smartphone ownership in this setting [45], we did not expect many HSAs to drop out. We believed that recruiting 102 HSAs would be sufficient to accommodate potential dropout, to ensure we achieved our desired sample size. Power calculations were computed using the “Power and Sample Size” option in Stata v. 13 (StataCorp, College Station, TX, USA) [46] which is appropriate for rates, specifically “*longitudinal studies, where the same cases serve as their own controls over time*” [47].

A total of 300 parents/caregivers whose children were referred to a higher-level facility or re-consulted at a village clinic completed the PCQ. It was estimated that approximately 600 children would be eligible for referral to a health care facility assuming: a 1% referral rate among 4000 children in the control group (*n* = 40), a 7–8% referral rate (change 6–7% from the initial 1% referral rate) among the same number of children in the intervention group (*n* = 300) and a 6–7% under-referral rate in the control group (*n* = 260). Considering the challenges in identifying those who were referred but did not present at a health care facility, or those who were not referred but did visit a health care facility or represented at a village clinic, and the possible withdrawal or loss to follow-up of parents/caregivers, it is estimated that at least half (*n* = 300) of the eligible cases will be followed up as part of the cost evaluation.

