#### Statistical/analysis methods

Primary outcome data will be evaluated using pairwise comparisons during the control and intervention periods. Analyses will be conducted at the level of the HSA, taking into consideration the number of index visits that occurred during each period, and will include descriptive statistics relating to each outcome (i.e., referral, re-consultation and hospitalization rates); tests of differences by control/intervention period, and multivariate modeling to allow for adjustment of potential confounding factors within each period. Bivariate descriptive statistics will present proportions for categorical variables or means/standard deviations for continuous and categorical data (respectively), for control/intervention periods. Measures of change will be calculated and two-proportion z-tests or chi-square tests will be used to measure unadjusted differences (depending on test assumptions met). We will conduct multivariate analysis using linear regression to evaluate change in outcomes adjusted for composition of children at each HSA by age, gender, symptoms, location (urban/rural) and proximity to the nearest higher-level health facility. For these models, assumptions will be tested, transformations of variables will be made if needed, and a-priori confounders will be evaluated for inclusion in models. Effect modification will be tested by interactions with age and gender. A secondary analysis will be done at the level of the child adjusting for HSA as a cluster variable. Potential confounders and effect modifiers will also be tested in these models. Data analysis and reporting will be conducted with Consolidated Standards of Reporting Trials (CONSORT) [51].

A cost-consequence analysis will be conducted to report the costs and consequences under the control and intervention. All costs of seeking and receiving care for the control and intervention groups will be calculated separately in a disaggregated way at the household level. Direct costs (e.g., out-of-pocket payments and transportation costs), indirect costs (e.g., costs of parent/caregiver productivity loss) and consequences (e.g., hospitalization days) collected through the PCQ will be compared between parents/caregivers enrolled in the control and intervention phases.

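### The leading test of effect modification by age and gender sits in an HSA-level regression, where it compares HSAs by caseload mix and not children by age or sex

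*Protocol article*

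**What the plan says.** All the relevant text is in the Statistical/analysis methods section, in this order.

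- On the unit for the primary outcomes: "Analyses will be conducted at the level of the HSA, taking into consideration the number of index visits that occurred during each period".
- On the multivariate model: "linear regression to evaluate change in outcomes adjusted for composition of children at each HSA by age, gender, symptoms", followed by location and proximity to the nearest higher-level facility.
- After a sentence on checking the assumptions of these models: "Effect modification will be tested by interactions with age and gender".
- Only then: "A secondary analysis will be done at the level of the child adjusting for HSA as a cluster variable".
- On those child-level models: "Potential confounders and effect modifiers will also be tested in these models".

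The section does not say which of the two sets of interaction tests carries the conclusion. It does not name the modifiers again for the child-level model, and it does not say whether a child's age or sex is to be separated into within-HSA and between-HSA parts.

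**The concern.** When the response is change per HSA and the covariate is that HSA's share of girls or mean age, the null hypothesis is that an HSA's change is unrelated to its caseload mix. The clinical question is whether the App effect differs between girls and boys, or between younger and older children. The first is an ecological hypothesis and the second an individual one.

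Two things follow. Every HSA sees both sexes and a range of ages, so much of the information on these modifiers lies within HSAs, and aggregation discards it. What remains is a comparison between HSAs, which is open to any HSA characteristic that goes with caseload mix.

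At stake is how a subgroup statement is read. A null result from the leading model would be weak evidence that the App works alike in all children. A positive result might reflect the HSAs and not the children.

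**Working it through.** **The plan's own figure.** The article gives no power for the interaction. Its nearest figure, in Sample size, is that "97 HSAs would provide 80% power for a minimum detectable rate of change between 6 and 7" percent, one-sided at alpha 0.05. A paired-proportions formula with the HSA as unit and all discordance in one direction (an assumption) is n = (1.645√d + 0.842√(d − d²))²/d². It gives 101 at d = 0.060, 98 at 0.0623, 94 at 0.065 and 87 at 0.070. The figure of 97 is therefore reproduced within the stated range. It concerns the overall change and says nothing about interactions.

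**Inputs from the article.** 102 HSAs; 8000 children, about 4000 per period; control referral rate 1%; change of 6 to 7 points, taken as 6.5. Children per HSA per period: 8000/(102 × 2) ≈ 39.

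**Assumptions, because the article gives none.** Half the children are girls. The true effects by sex are +5 v +8 points or +4 v +9 points (both average 6.5). The share of girls varies between HSAs by chance alone, or with an extra SD of 10 points. Tests are two-sided at 5%.

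**HSA-level test: regress change on share of girls**

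- Residual SD of one HSA's change: √(0.01 × 0.99/39 + 0.075 × 0.925/39) = 0.045.
- SD of the share of girls by chance over 78 children: √(0.25/78) = 0.057. With the extra 10 points: √(0.10² + 0.057²) = 0.115.
- SE of the slope = residual SD/(SD of mix × √102): 0.045/(0.057 × 10.1) = 0.079 for chance variation, and 0.045/(0.115 × 10.1) = 0.039 with the extra spread.

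**Child-level test: period × child's sex, about 2000 children per sex per period**

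- +4 v +9 points: SE = √[(2 × 0.01 × 0.99 + 0.05 × 0.95 + 0.10 × 0.90)/2000] = 0.0089, z = 0.05/0.0089 = 5.6.
- +5 v +8 points: SE = √[(2 × 0.01 × 0.99 + 0.06 × 0.94 + 0.09 × 0.91)/2000] = 0.0089, z = 0.03/0.0089 = 3.4.

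| Assumed effects | HSA level, mix by chance | HSA level, extra SD 10 points | Child level |
|---|---|---|---|
| +5 v +8 | z = 0.38, power 7% | z = 0.77, power 12% | 92% |
| +4 v +9 | z = 0.63, power 10% | z = 1.29, power 25% | over 99% |

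Simulation of the same scenarios gives 7 to 24% at HSA level and 91 to 100% at child level. With mix varying only by chance, the variance ratio is (0.079/0.0089)² ≈ 79, so aggregation keeps little more than 1% of the information. A separate simulation with +4.5 v +8.5 points gave HSA-level power of 11%, 12%, 17% and 32% for extra mix SDs of 0, 5, 10 and 15 points, against 98 to 100% at child level.

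**Rejection when the effect is the same in both sexes**

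- No link between HSA effects and mix: the HSA-level test rejected in 5.8 to 7.2% of 500 runs, close to nominal.
- HSA effects with SD 2 to 3 points, correlated 0.3 with mix (both assumed): about 18 to 33% across two simulations. A within-HSA child-level comparison rejected in 4 to 5%.
- A deliberately strong link (3 points of effect per 10 points of mix), with mix SD 5, 10 and 15 points: the HSA-level test rejected in 59%, 100% and 100%. A child-level interaction not split into within and between parts rejected in 5%, 24% and 76%. The split version stayed at 4 to 6%.

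The last item shows why the within-HSA contrast matters in the child-level model too.

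**The case against.** The strongest objection is that the test asked for is already planned. The child-level analysis also tests effect modifiers, and age and gender are the only ones the section names. A reader might infer from the HSA-level wording that the trial would miss real effect modification, or would report that there is none. The document does not support that. Both models are to be run, the child-level one has high power in the scenarios above, and nothing says that a non-significant HSA-level interaction will be reported as absence of modification. This part of the objection stands and limits the point to which test leads.

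The false-positive concern is conditional. It needs HSA effects that correlate with mix, and the planned adjustment for symptoms, location and proximity may remove part of that. Such a rejection is also not a Type I error for the HSA-level null, because change is then really related to mix. It is an error of interpretation. This stands as well.

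It can also be said that the article gives no formula. In a regression of change, the mix coefficient is itself the modification term, and rates per HSA could be computed within sex or age strata, which would keep the within-HSA information. Exact terms may be left to the statistical analysis plan. But the article does state that age and gender enter as the composition of each HSA's children, and it places the interaction sentence with that model. A period × mix term fitted to HSA rates from both periods would make the same between-HSA comparison. The problem is the level at which the leading test is stated, not missing detail.

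Finally, effect modification is not among the objectives or outcomes. That bears on severity, not on whether the test matches the question.

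**Conclusion.** The point holds in limited form. As worded, the leading interaction test addresses caseload mix, not a child's age or sex. For sex, under the assumed effects and an extra mix SD of 0 to 10 points, its simulated power is about 7 to 24%, against more than 90% at child level. It keeps close to nominal size unless HSA effects correlate with mix.

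The figures rest on assumed effect differences and an assumed spread of mix. They cover sex only. The same aggregation argument applies to age, but the article gives nothing on how age mix varies between HSAs, so no figure is offered. The simulations include no secular trend.

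The planned child-level analysis reduces the consequence. It does not remove it, because that analysis is labelled secondary, is given no precedence for this question and states no within-HSA contrast. The primary overall comparison is unaffected. This is a minor-to-moderate point.

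**What to change.** State in Statistical/analysis methods that effect modification by age and gender is judged in the child-level model already planned, as period × child's age and period × child's sex. Specify within-HSA contrasts, either by centring the covariates on the HSA mean (with the HSA mean and its interaction with period as separate terms) or by including HSA effects with the contrast formed within HSA. Drop the age and gender interactions from the HSA-level regression, or label them an exploratory caseload-mix analysis that does not bear on individual effect modification.

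The cost is one or two sentences. A child-level model is already planned, and the child's age and gender are already intended as covariates, so no new data are needed. The sample size and the primary comparison stay as they are.

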Utilizing mobile health (mHealth) technologies (e.g., smartphones, tablets) to deliver CCM could encourage the dispensation of more appropriate treatment recommendations [25] thereby increasing urgent referral rates. Potential improvements may be underpinned by a combination of better control of how the end-user navigates through assessment questions (e.g., built-in validation rules forcing completion of relevant fields with valid data before advancing to the next field/screen) [26]; enhanced CHW motivation linked to the prestige of using advanced technology in a predominantly paper-based health care system; automated presentation of the next-steps reducing reliance on memory [27], and heightened perceived efficacy and caregiver trust in CHWs’ decisions linked to clearer explanations about the child’s condition and recommended treatment [27].

Despite the opportunities that mHealth may afford for circumventing some of the limitations of current paper-based delivery [26], there is a paucity of evidence demonstrating the comparative benefits of deploying digitized versions of CCM on health service utilization and associated patient costs. To address this evidence gap in a pragmatic cluster-randomized trial, we will evaluate the added value of an electronic CCM App (truncated to SL eCCM App) developed as part of the Supporting Low-cost Interventions For disEase control (Supporting LIFE) program. As well as contributing to the broader mHealth literature, we anticipate that trial findings will provide Malawi’s mHealth Working Group with empirical data, which can be used to inform policy regarding the opportunities to Malawi of introducing such interventions for CCM. Our hypothesis is that adding the SL eCCM App to sick child assessments will increase urgent referral rates and reduce re-consultation and hospitalization rates.

The main objectives of this trial were to determine the:▪ Added value of the SL eCCM App (used with paper-CCM) on referral, re-consultations and hospitalization rates among acutely unwell children aged under 5 years, compared with paper-CCM alone▪ Factors influencing caregivers’ decisions to comply with urgent referral recommendations▪ Direct and indirect costs to caregivers presenting to higher-level facilities and/or re-attending village clinics after the index visit when using paper-CCM and the paper-CCM + SL eCCM App

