#### Other outcomes

▪ HSA and caregiver-perceived barriers and facilitators to caregiver compliance with urgent referral recommendations▪ Direct and indirect costs to caregivers of planned and unplanned re-consultations and urgent referrals to any type of health facility (i.e., health centers, community/rural and district hospitals)▪ HSA and caregiver attitudes towards the SL eCCM App and the intervention experience

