A subgroup of caregivers, recruited in both the control and intervention phases, who returned to village clinics or who took their child to a higher-level health facility (irrespective of whether an “urgent referral” recommendation was given at the index visit), were asked to complete a Patient Costs Questionnaire (PCQ). The survey was adapted from the Cooking and Pneumonia Study (CAPS) implemented in Malawi [41] and collected sociodemographic details (e.g., level of education, marital status, occupation), financial (e.g., cost of transportation, medication) and time-related (e.g., duration of travel) costs associated with seeking subequent health care for their child. Where practical, survey data was collected from caregivers over the telephone, or, obtained in person in the community with the assistance of the recruiting HSA. Because we anticipated mixed literacy levels among the patient population, the survey was completed either by the caregiver, or by a member of the study team fluent in the local language, who read the questions and scribed on behalf of caregivers. A convenience sample of enrolled HSAs and caregivers from each cluster participated in a semi-structured interview 1–2 weeks after the intervention (HSAs) or recruitment (caregivers), respectively. One-to-one interviews were conducted in person (or depending on location/availability of caregivers, over the telephone) by a member of the study team fluent in the primary language of participants. This interview format was selected due to the influence that cultural factors (e.g., collectivism, gender and sociodemographic inequities) could have on openness of communication in group interviews [42]. Tailored, semi-structured topic guides were used to facilitate interviews and included questions relating to perceptions of the barriers and facilitators to caregiver compliance with urgent referral recommendations and the perceived impact of the SL eCCM App. Topic guides were developed by the study team and were informed by nascent research related to challenges of accessing health care in LMICs, and from findings from focus groups held as part of the feasibility study. All interviews were audio-recorded, lasted between 30 and 40 min, and were held in private. Data collection instruments and/or interview guides can be made available upon request to the corresponding author.

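### The planned cost comparison covers only caregivers who sought further care, so it cannot show cost effects that arise through how many seek care

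*Protocol article*

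**What the plan says.** The protocol article deals with costs in five places.

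- **Background, objectives.** The cost objective is "Direct and indirect costs to caregivers presenting to higher-level facilities and/or re-attending village clinics after the index visit", under paper-CCM and under paper-CCM plus the App. The hypothesis in the same section is that "adding the SL eCCM App to sick child assessments will increase urgent referral rates and reduce re-consultation and hospitalization rates".
- **Other outcomes.** The cost outcome is "Direct and indirect costs to caregivers of planned and unplanned re-consultations and urgent referrals to any type of health facility".
- **Follow-up.** The PCQ is given, in both phases, to a subgroup of caregivers "who returned to village clinics or who took their child to a higher-level health facility", whether or not the child was urgently referred. Separately, recruited caregivers in both phases are contacted at two weeks and asked about re-attendances, presentations and hospitalizations.
- **Sample size.** "A total of 300 parents/caregivers whose children were referred to a higher-level facility or re-consulted at a village clinic completed the PCQ". The 300 is taken as half of about 600 eligible children, a total built partly from "a 1% referral rate among 4000 children in the control group".
- **Statistical/analysis methods.** Costs "will be calculated separately in a disaggregated way at the household level". Direct costs, indirect costs and consequences such as hospitalization days "collected through the PCQ will be compared between parents/caregivers enrolled in the control and intervention phases".

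The article does not plan a cost per enrolled child, a zero cost for followed-up children with no further care, or a correction for the fraction of care-seekers who complete the PCQ.

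**The concern.** Seeking further care happens after the child has been assessed with or without the App, and the hypothesis is that the App changes how often it happens. Restricting the comparison to care-seekers has two consequences.

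First, any cost effect that works through the number of caregivers who travel, pay and lose working time drops out, because only those who did so are compared.

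Second, the care-seekers in the two phases may be different kinds of children. If the App refers less severe cases, for example, the average visit changes because the mix changed. Randomizing the crossover times does not protect a contrast among care-seekers.

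The result is meant to describe costs and consequences under control and intervention, and the Discussion offers the trial's findings to decision-makers. A reader could take equal cost per care-seeker to mean that the App has no cost implication for caregivers. A reader could also take fewer hospital days per care-seeker as a benefit when only the denominator grew.

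**Working it through.** **Step 1: the plan's own figure.** Inputs from Sample size: 4000 children per phase, referral of 1% in control and 7–8% in intervention, and under-referral of 6–7% in control.

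- Control referrals: 0.01 × 4000 = 40.
- Intervention referrals: 0.075 × 4000 = 300 (range 280–320).
- Under-referred in control: 0.065 × 4000 = 260 (range 240–280).
- Sum: 40 + 300 + 260 = 600, and half is 300. The stated figures reproduce.
- By phase, the eligible pool is 40 + 260 = 300 in control and 300 in intervention.

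**Step 2: cost per care-seeker against cost per enrolled child.** Let p be the referral rate, a the share of referred children who are taken for care, and b the share of non-referred children who seek care anyway. Then

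- share seeking care: S = p·a + (1 − p)·b;
- cost per enrolled child = S × mean cost per care-seeker.

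The article fixes neither a nor b for this trial. Background cites non-completion of over 50% in sub-Saharan Africa. I assume a = 30–100% and b = 0–10%, with b and the mean cost per care-seeker the same in both phases. The planned comparison then gives a ratio of 1.0 throughout. The ratio per enrolled child is S(intervention) / S(control), shown here for p = 7% to 8% against 1%:

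| a | b = 0 | b = 2% | b = 5% | b = 10% |
|---|---|---|---|---|
| 30% | 7.0–8.0 | 1.74–1.86 | 1.29–1.33 | 1.12–1.14 |
| 50% | 7.0–8.0 | 2.16–2.35 | 1.50–1.58 | 1.23–1.27 |
| 80% | 7.0–8.0 | 2.68–2.96 | 1.78–1.91 | 1.39–1.46 |
| 100% | 7.0–8.0 | 2.97–3.30 | 1.96–2.12 | 1.50–1.58 |

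Worked cell, a = 50%, b = 5%, intervention p = 7.5%:

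- control: 0.01 × 0.5 + 0.99 × 0.05 = 0.0545, or 218 per 4000;
- intervention: 0.075 × 0.5 + 0.925 × 0.05 = 0.08375, or 335 per 4000;
- ratio: 0.08375 / 0.0545 = 1.54.

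**Step 3: the offset.** The table holds b constant, whereas the hypothesis expects fewer re-consultations and hospitalizations. In the worked cell, the extra cost vanishes if b in the intervention phase falls to (0.0545 − 0.0375) / 0.925 = 0.018, that is from 5% to about 1.8%. A larger fall would make cost per enrolled child lower under the App. The planned ratio stays at 1.0 in every case.

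**Step 4: hospital days.** Take the worked cell and suppose total hospital days D are identical in the two phases. Days per care-seeker are D/218 in control and D/335 in intervention. The ratio is 218/335 = 0.65, a fall of about 35% that comes only from the larger number of care-seekers.

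**The case against.** **The analysis matches its objective.** The objective in Background is worded for caregivers who present or re-attend, and the outcome, the PCQ sample and the analysis follow it. This stands. A reader might infer that the plan fails its own objective, but the text does not support that. Cost per care-seeker is a legitimate description. What it cannot do is stand for the cost effect of the App.

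**Care-seeking volume is reported elsewhere.** Referrals, completed referrals, self-referrals, re-consultations and hospitalizations are main outcomes, and Statistical/analysis methods compares referral, re-consultation and hospitalization rates by phase. The cost-consequence format is disaggregated by design. So the trial does not overlook how many seek care. The remaining gap is that no step joins rates and costs, and PCQ sampling within phase and visit type goes uncorrected.

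**The effect may be small.** A reader might compare 40 with 300 referrals and infer a 7.5-fold rise in caregiver costs. That needs every care-seeker to be a referred child, whereas the PCQ also covers re-attenders and self-presenters. It also leaves out the 260 under-referred control children, with whom the eligible pool is 300 in each phase. Those 260 are not confirmed care-seekers, so a ratio of 1.0 is not established either. The several-fold rise that the plan assumes is in referral recommendations, not in care-seeking.

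**The analysis plan may cover this.** The article promises a full statistical analysis plan, and zero handling, weighting and model form could be left to it. That is fair for those details. The data source and the between-phase contrast, however, are already fixed in the article.

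**Conclusion.** The point holds as a limitation of the between-phase cost comparison. It conditions on a post-exposure event, cannot show cost effects that act through the number seeking care, and is open to case-mix differences between phases.

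Its size depends on assumptions. With equal cost per care-seeker, unchanged care-seeking among non-referred children and the plan's 1% against 7–8% referral, the ratio per enrolled child runs from about 1.1 to 8 where the planned ratio is 1.0. The top of that range needs no care-seeking at all by non-referred children. Fewer re-consultations or hospitalizations would lower the ratio, and the documents fix neither its net size nor its direction. A reader might infer that the planned analysis will give the wrong sign on cost, but nothing in the documents shows that. The 35% fall in hospital days per care-seeker is an illustration at 50% completion and 5% care-seeking, not a forecast.

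This concerns a secondary outcome and leaves the primary analysis untouched. The change is still worth making, because a better contrast can be built from data already sought.

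**What to change.** For the between-phase cost-consequence comparison, report mean cost and mean hospital days per enrolled child with follow-up:

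- assign zero to followed-up children with no further care;
- weight PCQ respondents by the inverse of the fraction of care-seekers surveyed, within phase and visit type;
- estimate the phase difference with cluster and calendar time in the model;
- keep cost per care-seeker as a descriptive result, placed beside the utilization rates and labelled as conditional on seeking care.

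No new data collection is planned for this, since care-seeking is already asked of recruited caregivers in both phases at two weeks. It does carry costs. The data will be skewed with many zeros, so a bootstrap or two-part model is needed. The weights need counts of care-seekers and PCQ respondents by phase and visit type, and the article states no rule for choosing the subgroup. The zeros rest on caregiver reports and incomplete records. Data management says that missingness at random cannot be assumed, so the result applies to followed-up children and should be reported with follow-up rates by phase.
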